## Methods

### Study design

MET-FINGER is a randomised, controlled, parallel-group, multicentre phase-IIb proof-of-concept clinical trial testing the FINGER 2.0 multimodal lifestyle-based intervention, including a pharmacological trial-within-trial with metformin (Fig. 2). The participants will be first randomised 1:1 to the FINGER 2.0 intervention (SMLI for all participants + metformin where appropriate; active arm) or the SGMI (regular health advice; control arm). Participants allocated to the FINGER 2.0 intervention, and with indicators T2D risk, but no diagnosed/suspected diabetes, will be randomised 1:1:1 to receive metformin 2000 mg/day, metformin 1000 mg/day, or placebo, together with the SMLI. Participants allocated to the FINGER 2.0 intervention but not eligible for metformin treatment will receive the SMLI alone. At each site, both randomisation steps (Fig. 2) are carried out using a computer-generated list from the OpenClinica database. In each randomisation step, the list is stratified by site and programmed using random blocks of various sizes.

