### Participants

Six hundred participants will be included across three sites to obtain an *APOE* ε4-enriched population (≥ 50%).

In the United Kingdom (UK), participants (*n* ~ 300) will be recruited at Imperial College London (ICL) from the Cognitive Health in Ageing Register: Investigational, Observational and Trial studies (CHARIOT). In Finland, participants (*n* ~ 200) will be recruited via the Finnish Institute for Health and Welfare (THL) biobank. In Sweden, participants (n ~ 100) will be recruited from the electronic database and biobank for clinical dementia research at Karolinska University Hospital (KUH) Theme Inflammation and Aging, Theme medical unit (GEDOC).

Within the relevant registries, potential participants will be first invited for Screening for Lifestyle (Fig. 2) based on age and other eligibility criteria, depending on data availability. Eligible participants will be further invited to participate in the full study. At all sites, participants for whom *APOE*-genotype data is available will be invited for screening starting with an approximate 50/50 ε4 carrier/non-carrier ratio. Carriers have at least one ε4-allele. To ensure 50% minimum enrichment in the overall trial cohort and a similar carrier/non-carrier ratio at all sites, carrier/non-carrier ratio within the eligible population is regularly monitored to adjust the proportion of ε4 carrier/non-carrier invited. The site-stratified randomisation ensures a similar carrier/non-carrier ratio in the two groups at all sites. If needed, participants may be newly genotyped. At Screening for Lifestyle, participants can request disclosure of their APOE genotype. Other recruitment sources (e.g. media campaign) may be used if needed to reach the recruitment target.

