### Statistics

The trial primary comparison is Self-Guided versus FINGER 2.0 multimodal intervention arm, and the trial has been powered for this purpose. Power calculations for the primary outcome are based on FINGER data. FINGER included 1260 participants (~ 33% *APOE* ε4 carriers), with an overall drop-out rate of 12% during the 2-year intervention. We estimate that a smaller sample size would be sufficient for MET-FINGER, based on (i) *APOE* ε4 enrichment at least 50% (stratified analysis of FINGER data indicated intervention benefits especially among ε4 carriers); [25] (ii) potential added benefit of metformin; and (iii) optimization of the initial FINGER lifestyle intervention. In FINGER, the observed mean 2-year change (SD) in primary outcome among *APOE* ε4 carriers was 0.10 (0.38) in the control group, and 0.19 (0.34) in the intervention group. A sample size of 506 participants would be needed to demonstrate a between-group difference with 80% power and at 5% significance level. Assuming a 15% drop-out over 2 years, a total sample size of 600 participants would be required.

The primary efficacy analysis will be based on the modified intention-to-treat population, including all randomly assigned participants with baseline and at least one post-baseline observation.

Appropriate transformation to skewed NTB components will be applied. Mixed-effects regression models with maximum likelihood estimation will be applied to analyse change in cognitive scores, as a function of randomization group, time, and group × time interaction. The site will also be included in the model as fixed effect. Non-linearity of change will be taken to account. The other secondary endpoints will be analysed using the appropriate generalised mixed-effects regression model depending on the outcome distribution.

Potential heterogeneity of intervention effects will also be investigated in subgroup analyses, for both primary and secondary outcomes by, e.g. demographics, *APOE* ε4 carrier status, baseline cognitive and functional level, and intervention adherence, although the trial is not powered for such analyses.

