For most exploratory outcomes of the lifestyle + metformin trial-within-trial, the same model in the primary analysis of the trial will be used for continuous outcome variables; for categorical outcome variables (e.g. adherence-related outcomes) logistic regression models will be applied. For retention rate and target metformin dose, chi-2 test will be used to compare the three arms.

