#### Metformin/placebo treatment

The study-drug treatment will be conducted double-blinded. All participants receiving the SMLI (*n* ~ 300) who are eligible for metformin treatment (Table 1; estimated rate based on data from recruitment sources = 50%, unpublished) will be randomised to either: metformin 2000 mg/day, metformin 1000 mg/day, or placebo.

Metformin will be administered as Glucophage®XR 500 (“SR” in the UK), in form of 500 mg oral tablets. The placebo is prepared based on Glucophage® SR/XR specifications. The placebo will be manufactured to be identical to the active tablets. Both metformin and placebo will be manufactured in bulk by Merck KGaA (Darmstadt, Germany) and prepared at Guy’s and St Thomas’ NHS Foundation Trust Pharmacy Manufacturing Unit (London, UK) in identical dispensing packs, containing sufficient tablets for 3 months. To obtain the target dose, a blinded system will be in place to allow participants to take four tablets/day as follows:2000 mg/day 4 × Glucophage® SR/XR 5001000 mg/day 2 × Glucophage® SR/XR 500 + 2 × placeboPlacebo 4 × placebo

Participants are recommended to take all four daily tablets together with the evening meal. Gastrointestinal disorders are the most common adverse events; the extended-release formulation will be used to decrease such risks. Additionally, since these undesirable effects occur most frequently during therapy initiation, resolve spontaneously in most cases, and can be reduced by gradual dose increase, the study drug will be titrated from one tablet/day adding one tablet/day each week until the target dose is reached. If the target dose cannot be achieved, participants will be first instructed to reduce the dose to two tablets/day (half-dose) and if the half-dose cannot be achieved, the study-drug treatment will be discontinued.

Based on the safety profile of metformin, the treatment will be discontinued if it is deemed unsafe for the participant due to an adverse event/serious adverse event associated with the treatment (e.g. anaphylaxis, vitamin B12 deficiency); any severe adverse event considered to be related to the study treatment is reported; signs of hypersensitivity are reported; the participant develops diabetes; eGFR < 60 mL/min.

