Overall, findings from MET-FINGER and other ongoing placebo-controlled metformin RCT in MCI (NCT04098666) will inform decisions on future phase III precision prevention trials, including, e.g. selection criteria (both metformin eligibility criteria and criteria related to increased lifestyle-based and/or genetic dementia risk); metformin dose selection for combination with lifestyle intervention; and overall trial design, based on the target at-risk population and evidence-based estimates for power calculations, e.g. 3- or 4-arm design [58].

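### The chi-square test for retention and target metformin dose leaves out site, which stratifies the second randomisation; it stays valid but is mildly conservative and slightly less powerful if sites differ strongly

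*Protocol article*

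**What the plan says.** The Statistics section of the protocol article ends with the exploratory outcomes of the metformin sub-trial. Continuous outcomes mostly reuse the primary model. Of that model the article says: "The site will also be included in the model as fixed effect". For other outcomes, "for categorical outcome variables (e.g. adherence-related outcomes) logistic regression models will be applied"; the covariates of those models are not given. Two outcomes are then treated separately: "For retention rate and target metformin dose, chi-2 test will be used to compare the three arms". Neither site nor dose order is mentioned for this test.

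Under Study design, eligible participants "will be randomised 1:1:1 to receive metformin 2000 mg/day, metformin 1000 mg/day, or placebo", and on how the lists are built: "In each randomisation step, the list is stratified by site and programmed using random blocks of various sizes". Site is therefore a stratum of the randomisation that created the three arms being compared.

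Retention and target dose are listed as exploratory outcomes. The Limitations section says that the trial's findings should inform, among other things, "metformin dose selection for combination with lifestyle intervention".

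**The concern.** A comparison of randomised arms is normally analysed with the factors that stratified the randomisation. The plan does this in the primary model and, by reuse, for most continuous exploratory outcomes. For retention and target dose it names a test that has no place for a covariate. The sentence before it names a method, logistic regression, that could have carried site, and target metformin dose appears in the outcome list as an adherence item. No reason is given for the departure.

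Stratified randomisation balances the arms within site. If retention or dose achievement also differs between sites, a test that ignores site counts that variation as noise. Its true error rate then falls below the nominal 5% and some power is lost. With about 50 per arm there is little to spare, and these outcomes bear on a stated purpose of the sub-trial.

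**Working it through.** **Inputs from the protocol article**
- Sub-trial size: about 300 in the FINGER 2.0 arm, with the share eligible for metformin given as "estimated rate based on data from recruitment sources = 50%, unpublished". 300 × 0.50 = 150, and 150 / 3 = 50 per arm.
- Site shares: "In the United Kingdom (UK), participants (*n* ~ 300) will be recruited", with about 200 in Finland and about 100 in Sweden. Shares of 1/2, 1/3 and 1/6 of 50 give about 25, 17 and 8 per arm.

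**Plan's own figure.** None is given for these outcomes. The only sample size is for the primary outcome, and it reproduces: SD = √((0.38² + 0.34²)/2) = 0.361, difference 0.19 − 0.10 = 0.09, two-sided 5% and 80% power give 253 per arm by the t-test, or 506. Then 506 / 0.85 = 595.3, so 596, against 600 stated. It has no bearing on this point.

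**Assumptions**
- Each outcome is binary, so three arms give 2 degrees of freedom. The article does not say this.
- Arm rates (placebo / 1000 / 2000 mg/day) are as listed in the table.
- Site shifts on the log-odds scale: none; moderate (0.5, 0, −0.5; odds ratio between extreme sites e¹ ≈ 2.7); strong (1, 0, −1; odds ratio e² ≈ 7.4). Overall arm rates are held at the listed values.

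**Tests compared**, both at 5%, 20,000 simulated trials per scenario (Monte Carlo standard error at most √(0.25/20,000) ≈ 0.35 points):
- Pearson: X² = Σ (O − E)²/E over the 3 × 2 table, sites pooled.
- Cochran-Mantel-Haenszel (CMH), 2 df: Q = D′V⁻¹D, where D is observed minus expected counts in two of the arms, summed over sites, and V is the sum of the within-site hypergeometric covariances.

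**Rejection rates at 50 per arm (25/17/8), Pearson → site-stratified CMH**

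| Arm rates, % | No site effect | Moderate | Strong |
|---|---|---|---|
| 85/85/85 (null) | 0.050 → 0.049 | 0.047 → 0.049 | 0.039 → 0.051 |
| 90/85/80 | 0.215 → 0.213 | 0.213 → 0.217 | 0.205 → 0.235 |
| 90/80/70 | 0.615 → 0.613 | 0.614 → 0.622 | 0.614 → 0.661 |
| 95/85/75 | 0.744 → 0.737 | 0.745 → 0.746 | 0.749 → 0.778 |
| 90/90/70 | 0.781 → 0.781 | 0.779 → 0.784 | 0.787 → 0.816 |
| 90/70/70 | 0.733 → 0.732 | 0.738 → 0.746 | 0.734 → 0.778 |

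- Type I error of the chi-square under strong site differences: 3.9%, against 5.1% for CMH. At 40 and 60 per arm it is 3.5% and 4.1%. With a different layout of equally large shifts (−1, 0.3, 1) it was 3.3%, against 4.7% for CMH.
- Power gained by stratifying under strong site differences: 2.9 to 4.7 points at 50 per arm, and 1.5 to 5.9 points over 40 to 60 per arm.
- With no or moderate site differences: −0.7 to +0.8 points at 50 per arm, which is practically nothing.

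**Dose order, checked separately** (no site effect, 50 per arm, chi-square versus linear trend test): 90/80/70 gives 0.62 versus 0.72; 90/90/70 gives 0.78 versus 0.77; 90/70/70 gives 0.73 versus 0.68; 85/75/85 gives 0.24 versus 0.03.

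**The case against.** The strongest reply is that nothing here is invalid. A chi-square across three randomised arms answers the question asked, and its error is on the safe side. The outcomes are exploratory, the trial is powered only for FINGER 2.0 against the self-guided arm, and no confirmatory claim rests on this test. The gain from stratifying is close to zero unless sites differ strongly, and the smallest site has only about 8 per arm. The binary outcome is also an inference: the dosing text allows target dose, half-dose or discontinuation, and a 3 × 3 table would have 4 degrees of freedom. All of this stands, and it keeps the point small. It does not remove the point, because the article names a specific test that departs from its own treatment of site, and stratifying cost no material power in any pattern tried.

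Three stronger readings are tempting, and the documents do not support them.
- **That the test gives false positives.** Ignoring a stratification factor makes it conservative.
- **That ignoring dose order wastes power.** This holds only for a roughly linear pattern. The trend test gains nothing if only the top dose differs, loses about 5 points at 90/70/70 (a monotone pattern), and almost fails if the pattern is not monotone. The article assumes no dose-response shape and says that the suitable dose is uncertain, so an unordered test is defensible.
- **That the plan will give no estimate for each dose.** The article names a test and excludes nothing; such reporting is commonly left to the full protocol or analysis plan, which is not shown.

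**Conclusion.** A minor efficiency and consistency point holds. As written, the comparison of retention and target dose ignores the stratum used in the randomisation. The chi-square is valid. If sites differ strongly, its true level is about 4% or slightly lower instead of 5%, and it gives up roughly 2 to 5 points of power; otherwise the loss is about 0 to 1 point. The size rests on about 50 per arm, site shares in the planned proportions, a binary outcome, and arm rates and site differences that are assumed throughout. With very large differences between arms, such as 90/50/10%, every test has power of about 1.00 and the choice does not matter.

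**What to change.** Replace the chi-square for these two outcomes with a Cochran-Mantel-Haenszel test stratified by site, on 2 degrees of freedom. The alternative is the logistic regression already named in the same section, with arm and site as terms. Report the site-adjusted difference of each dose versus placebo with a 95% confidence interval, since a three-arm test alone does not show which dose differs or by how much. A dose-trend test may be added if it is labelled supportive. If target dose is to be analysed in more than two categories, say so, because the degrees of freedom change.

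The cost is one sentence of analysis wording and no extra data. The small downside is sparse cells at the smallest site: with 8 per arm and an assumed 85% success rate, 8 × 0.15 = 1.2 failures are expected per arm. The stratified test pools over sites and kept close to its 5% level in the simulations, but a per-site breakdown there would carry little information.

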### Ethical and regulatory considerations

The study will be conducted in accordance with the Declaration of Helsinki’ and the International Conference on Harmonisation for Good Clinical Practice (ICH GCP E6). The study protocol and relevant documents were approved by: the Human Research Authority (HRA, London-Westminster Research Ethics Committee, reference number 22/LO/0053); the Medicines and Healthcare Products Regulatory Agency (MHRA) approval nr. CTA 19174/0429/001–0001 (UK); the Finnish Committee on Medical Research Ethics (Tukija), the Finnish Medicines Agency (Fimea), the Swedish Medical Products Agency (Läkemedelsverket), and the Swedish Ethical Review Authority (EPM), EU-CT Number: 2022–500438-27–01. For full-study enrolment, two separate informed consents will be obtained from each participant, the first for assessing eligibility (Screening for Lifestyle, Fig. 2) and the second for full trial participation (at baseline). If nominated and available, informed consent will be obtained from Study Partners, prior to any data being collected from them.

The trial has been registered at ClinicalTrials.gov (NCT05109169, first release 26th October 2021) and has been adopted onto to National Institute for Health and Care Research – Clinical Research Network portfolio (NIHR-CRN, IRAS ID:1004303).

Potential participants were involved in the study design, including revision of the study material, and are providing continuous feedback during the trial (Supplementary Material SM1).

### Publication, dissemination, and data availability

Any publication reporting data of the present trial will be compiled according to the CONSORT guidelines and checklist. Publications arising from the trial will be available preferably through Open Access. Data arisen from and samples collected during the trial will not be made publicly available but will be available for collaborative sharing, after the main results of the trial have been published, and upon application to and approval by the trial management group. Access is subject to the MET-FINGER legal framework. An access agreement will be prepared and signed by the involved parties.

## Intervention

### FINGER 2.0 multimodal intervention

#### Structured Multimodal Lifestyle Intervention (SMLI)

The SMLI is an updated version of the FINGER intervention designed to provide individually-tailored, recommendations, and support to improve participants’ overall cognitive impairment risk profile, implement healthy lifestyle changes, and promote healthy ageing. It includes five components: *diet*, *physical activity*, *cognitive training*, and *management of cardiovascular/metabolic risk factors* will be delivered through separate structured programmes (Table 4); *social engagement*, will be delivered through group meetings (e.g. for diet, cognitive interventions), structured groups exercise sessions, and by supporting interaction among participants (e.g. independent group exercise).

**Table 4 Tab4:** Overall summary and schedule of the Structured Multimodal lifestyle Intervention (SMLI) Included in the FINGER 2.0 Multimodal Intervention

SMLI structured programmes^a^	Activity	Study months																							
		**1**	**2**	**3**	**4**	**5**	**6**	**7**	**8**	**9**	**10**	**11**	**12**	**13**	**14**	**15**	**16**	**17**	**18**	**19**	**20**	**21**	**22**	**23**	**24**
**Diet**	Group sessions	X4 (1.5–2 h)						X1 (1.5–2 h)						X2 (1.5–2 h)											
	Individual consultations	X2 (45–60 min)											X1 (45–60 min)												
**Physical activity**	Resistance and balance training (gym)		Once a week; gradually increasing from 30–45 min to 30–60, 45–60, and 60 min (by month 6)																						
	Resistance and balance training (online)			Once a week (duration as above)					Twice per week (duration as above)																
	Independent aerobic exercise			2–4 times per week (30–60 min)					3–5 times week (depending on the number of group training sessions, to have 1 day of rest)																
**Cognitive intervention**	Group sessions				X6 (1–1.5 h)																				
	Independent training						72 sessions (10–15 min); frequency: 3 times a week						Break 3–6 months			72 sessions (10–15 min); frequency: 3 times a week									
**Monitoring of cardiovascular/metabolic risk factors**	Practical consultation			1						1									1						
	Medical consultation			1			1						1												

^a^ The intervention is administered by applying common principles and procedures across sites, but always based on the unique risk profile of individual participants. Additionally, recommendations for diet and management of cardiovascular/metabolic risk factors follow the local/national guidelines, leading to local adaptations and some differences in the way these two components are delivered across sites. Furthermore, when administering the intervention, daily life/habits, needs, living location/conditions and cultural/socio-economic context are considered, both at participant and site level, to ensure tailoring, and support adherence. Continuous communication and participant feedback at 12 months will also help address any potential adherence concerns during the study. Overall, this allows for a highly tailored but still sufficiently harmonised intervention within and across sites. Participants randomised to the SMLI are assigned to a specific Intervention Participation Group (*n* ~ 5–10) and group meetings/exercise session will be organised as much as possible to include the members of a specific Intervention Participation Group. If necessary due to logistics and time availability, participants can attend group meetings/sessions in other Intervention Participation Groups

The *dietary intervention* aims to achieve adequate nutrient intake through a balanced and varied diet. It is based on the local guidelines and the FINGER dietary model, including principles of the Mediterranean diet (higher consumption of fruits/berries and vegetables, fish, vegetable oils and vegetable-fat based margarine, whole grain products and pulses/nuts/seeds, and limited consumption of red meat), and adjusting for country-specific habits and recommendations. These are suitable for the general population and individuals who may have an increased risk of dementia due to, e.g. hypertension, dyslipidaemia, or impaired glucose metabolism. Special emphasis will be put on dietary factors more strongly associated with brain health (e.g. fish, vegetable oils, fruit, vegetables, on a food level; omega-3 fatty acids, folate, vitamin E, and various vitamins from vitamin B group, on a nutrient level). The risk of nutrient deficiencies and excessive alcohol intake will be individually addressed following local guidelines. The intervention will be built on dietary goals, also used to calculate the FINGER Healthy Diet Index as a secondary outcome (Supplementary Table 2).

Trained nutritionists/dietitians will deliver the intervention through individual counselling sessions and group sessions (Table 4). The delivery will be based on theoretical guides (e.g. Intervention Mapping) with emphasis on translating general (e.g. “fish twice a week”, Supplementary Table 2) and/or tailored (e.g. “I will replace breakfast cereal with porridge oats”) goals into concrete behaviours. The “Specific, Measurable, Achievable, Relevant, and Time-Framed” (SMART) [26] principle will be used with the Stages of Change and Social Cognitive theories for goal-setting. Motivational interviewing will be partly applied during the individual meetings, and all goals will be tailored to individual needs and capabilities.

The *physical activity intervention* is based on international guidelines. It includes an individually tailored and progressive resistance and balance training programme (Supplementary Table 3) in group sessions, complemented with independent aerobic exercise (Table 4). Its goal is to make permanent changes in daily physical activity, and it will be administered by a physiotherapist/professional trainer.

The resistance/balance training programme will be delivered in a hybrid on-site/online setting. The on-site/gym sessions will include exercises for the eight main muscle groups (Supplementary Table 3). Online sessions will take place reproducing similar exercises using, e.g. high-resistance elastic bands, and everyday tools normally found at home (e.g. chairs, bottles). For participants to independently control their training and calibrate the load during online sessions, the physiotherapists will guide and instruct them to use the Borg Rating of Perceived Exertion (RPE) scale [27] during the in-person sessions at the gym, based on objective measurements. Adherence to the resistance/balance training programme will be self-recorded by the participant in a specifically designed diary provided by the physiotherapist.

The physiotherapist/professional trainer will plan individual aerobic training programmes, based on each participant’s preferences, needs, and habits. The programme will be regularly revised and adapted as needed and intensity will be adjusted with the Borg RPE scale. Participants will be supported to set up groups to exercise together.

The *cognitive intervention* includes an introductory phase of six group training sessions, alongside, an individual training delivered through a web-based cognitive training programme (Table 4, and Supplementary Material SM2). The *cognitive intervention* includes an introductory phase of six group training sessions, alongside, an individual training delivered through a web-based cognitive training programme (Table 4). The six group meeting sessions are an expansion on the original FINGER cognitive intervention, and their content has been updated to improve motivation and adherence to the individual training through a behaviour change framework [28]. The support programme will provide instructions and guidance for the use of the software-based cognitive training programme, and general education on, e.g. cognition and ageing, risk factors affecting cognition, and strategies to support cognitive functioning. The independent cognitive training will focus on cognitive tasks measuring working memory, executive functions, mental speed, and episodic memory, but no test from the cognitive outcomes NTB is included (Supplementary Material SM2). It consists of a minimum of 144 sessions with an individually adjusted progressive increase in difficulty, delivered three times/week for 10–15 min/session. Two blocks of three tasks respectively are alternated between sessions. The training programme is accessible at home, but training will be offered at the study sites as needed.

The *cardiovascular and metabolic risk factor management intervention* aims to identify the onset of risk factors and support risk reduction. Country-specific evidence-based guidelines will be used at each site. Practical consultations will be conducted at 3, 9, and 18 months, either by a study nurse or a study physician. The consultations will include physical measurements (e.g. blood pressure, BMI) and a review of previous assessments, on which individually tailored feedback will be provided. Clinical/medical consultations will be organised at 3, 6, and 12 months with a study physician. Information on the management of dyslipidaemia; hypertension and diabetes; smoking; alcohol use; weight; as well as other health-related issues that influence the management of vascular risk factors will be provided. Participants will be referred to their primary healthcare provider (according to local healthcare settings) if the need for initiation or adjustment of pharmacological treatment is identified. No medications will be initiated as part of the trial, other than the tested metformin/placebo.

As needed, participants are supported to set and monitor goals to improve their risk profile and will be motivated to adhere to both the relevant lifestyle changes and pharmacological treatment they might have been prescribed by their treating physician.

